#### *Serious gaming and ADHD*

Serious games are also known as *social impact games* or *non-entertainment games*, meaning a game with a goal other than entertainment. A goal of a serious game could be for example education or training social skills. Gaming elements can be used to teach or convey a message in a fun and safe way. The entertaining character of games could be a motivation to use a serious game as a form of treatment. After all, games are challenging and fun to play, and it stimulates the player due to it's interactivity (Kranenburg, Slot, Staal, Leurdijk & Burgmeijer, 2006). Previous research has shown that interest and motivation of children with ADHD is positively influenced when learning tasks are offered in an attractive and interactive manner, such as a computer game (Emes, 1997; Tannock, 1997; Pfiffner, Barkley, Dupaul, 2006). Additionally, parents/legal guardians, teachers and clinicians report that while playing a computer game, children with ADHD have longer attention spans, are more concentrated and less impulsive (Barkley, 2006). Through giving frequent and direct reinforcement on a child's performance, optimising that performance will be stimulated.

Designing a serious game for children with ADHD is promising because children with ADHD appear to be motivated to play a computer game, and learn more this way, since they are more focused, more concentrated and less impulsive. Children with ADHD also tend to learn more effectively in an implicit way, though activities and experiences rather than studying books (Rosas et al., 2010). Because of this, it may be expected that children with ADHD could learn certain skills though an immersive and interactive serious game. A serious game which is tailored to meet the needs of these children could eventually lead to a decrease of associated problems in ADHD and complement the current treatment.

From a global search on the internet it appears that there are several ADHD games available online (see <http://www.fupa.com/games/1/adhd.html>). Unfortunately, these games have not been evaluated nor validated for the impact on outcomes. Some research has been done to examine the impact of games on attention span, relaxation and working memory in children with ADHD (Amon & Campbell, 2008; Pope & Bogart, 1996; Van der Oord, Ponsioen, Geurts, Brink, & Prins, 2012; Prins, DAVIS, Ponsioen, Ten Brink, & Van der Oord, 2011). Although these computerized interventions are also focused on the target group of children with ADHD their aim and format is very different compared to HealSeeker. Pope and Bogart (1996) try to modify attention deficits through an extended attention span training. When the player's brain wave indicates that attention is waning, the video game becomes more difficult so that attention from the player is re-initiated. Furthermore, the study of Amon and Campell (2008) is aimed to teach children with ADHD breathing and relaxation techniques through a game to diminish their disruptive behaviour patterns. Both studies are focused on reducing the core symptoms instead of associated problems of ADHD. Van der Oord and colleagues (2012) developed a neurocognitive training with three-dimensional game elements to attain the optimal level of performance on three executive functions (i.e. working memory, response inhibition and task switching). From the results it appeared that these skills are successfully trained in a timeframe of 12 hours. At the moment, this training is offered and examined in different target groups (i.e. autism and obesity). This implies that this training is not specifically designed for children with ADHD but for children who have difficulties with working memory.

### *Pilot Study Results*

Janssen-Cilag BV (pharmaceutical company) initiated the idea to develop a serious game for children with ADHD in close collaboration with Yulius Mental Health Care Organisation and Ranj (serious game developer). The first prototype of HealSeeker has not been created from a point of view of already existing training programs, but instead an innovative gaming environment was created. HealSeeker is aimed at reducing associated problems in the area of time management, planning and social functioning and teaching children strategies to deal with situations in which these skills are needed and thereby improving self-management. HealSeeker is specifically designed for children from 8 to 12 years old. This young group of children has a good learning capacity which enables these children to develop at high speed and thereby feel competent. Training skills concerning planning, time management and social behaviour in children with ADHD at a young age, might prevent problems at school, at home and in relations during puberty.

From October 2011 till March 2012 a pilot study was conducted to test several game elements of the prototype HealSeeker for usability, and to examine the direction of possible

learning effects. In total, 42 children with ADHD were included in the study. Children were randomly assigned to two play conditions: a high frequent play condition (children were asked to play a minimum of eight times per two weeks) and a low frequent play condition (children were asked to play a maximum of three times per two weeks). Children played the game for eight weeks, divided in four periods of two weeks. Children were asked to play the game for a minimum of 30 minutes and a maximum of 45 minutes per game moment. Parents/legal guardians and children filled out several questionnaires at pre- and post-test. Data analyses were performed using complete data of 36 children. Children's age ranged between 8 and 11 years with a mean age of 9.5 years. Twenty-six boys and 10 girls were included. From the results it appeared that parents/legal guardians were quite positive about the game. They rated HealSeeker with an average of 6.8 (range 6-10). Eighty-three percent of the parents/legal guardians would recommend this game to other parents/legal guardians of children with ADHD, once it is further developed. Ninety-four percent of the children liked to play HealSeeker. Preliminary results regarding the possible learning effects of HealSeeker provide an indication of therapeutic effects in the direction of improvement of time management and planning. Effects on social functioning could not be demonstrated. Intention to treat (ITT) analyses demonstrated similar results as the results stated above.

Based on these preliminary results, a final version of HealSeeker was developed. Specifically, the game was made more attractive and thereby thought to be more motivating and challenging for children. In addition, more learning situations were implicitly interwoven in game elements and the story line. A closed social community was included in which children could communicate with each other and ask each other for help through predefined messages.

## **2. OBJECTIVES**

### **2.1 Primary objective**

The primary objective of this study is to examine the effectiveness of HealSeeker for improving time management, planning and organisation and social behaviour skills of children with ADHD.

### **2.2 Primary research question**

Does HealSeeker improve skills in the area of time management, planning and organisation and social behaviour skills of children with ADHD from 8 to 12 years of age? The expectation is that playing the HealSeeker game will lead to significant improvements in skills in the areas of time management, planning and organisation and social behaviour skills compared to a control group condition.

Van der Oord and colleagues (2012) investigated the effects of an executive function training program with game elements in children with ADHD. Results are encouraging and show a significant reduction in both ADHD behavioural symptoms and executive functioning problems. Moreover, recent evidence shows that serious games can be valuable in mental health care, for example to learn certain behavioural skills (Douma, 2008; Kato, 2010). A study about the effects of a serious game on willingness to help and role taking showed that interactive digital games can enhance empathic reaction to social issues (Peng, Lee, & Heeter, 2010). In addition, multiplayer online role-playing environments contain methodologies of role-play, modelling, instruction and reinforcement and by doing so social skills can be practised (Martin, 2009). Healseeker also uses elements of modelling, reinforcement and co-operation. Healseeker is an innovative program that does not purely train working memory but learn children strategies to cope with their difficulties in the area of time management, planning and social behaviour. Motivating and engaging children through a game is expected to optimize performances in these areas.

### **2.3 Secondary objectives**

The secondary objective of this research is to examine the effects of Healseeker on working memory and self efficacy. In addition, it is examined whether intervention effects vary as a function of gender, age, ethnicity, SES, intelligence level, comorbidity, game experience, severity of psychopathology and satisfaction. The distribution of these baseline characteristics should be taken into account when answering this additional question.

## 2.4 Secondary research questions

- Does working memory serve as a mediating variable in the relationship between HealSeeker and outcome measures? The expectation is that playing the HealSeeker game will lead to significant improvements of working memory and that this will lead to improvements in outcome measures.

As mentioned earlier, working memory can be improved through computerized training programs. Improvements were also illustrated among other domains of executive functioning which supports the hypothesis that working memory is an intermediated factor in improving higher levels of executive functioning, for example planning and organisation skills (Beck, Hanson, Puffenberger, Benninger, & Benninger, 2010). Interestingly, Kofler and colleagues (2011) revealed a relationship between working memory deficits and social problems that was attenuated through its impact on ADHD symptoms. The core symptoms of ADHD, which can interfere with social behaviour, can be reduced by improving working memory capacity.

- Does self-efficacy serve as a mediating variable in the relationship between HealSeeker and outcome measures? The expectation is that playing the HealSeeker game will lead to significant improvements of self-efficacy and that this will lead to improvements in outcome measures.

Higher working memory capacity is positively related to self-enhancement (Schmeichel, 2010). There is evidence that games can improve self-efficacy of adolescents with cancer (Kato, Cole, Bradlyn, & Pollock, 2009). Additionally, it appears that neurofeedback and computerized attention tasks can positively influence self-management abilities of children with ADHD (Geuensleben et al. 2010). When children have higher levels of confidence in their skills this will eventually lead more effective learning (Bandura, 2006).

For more information about outcome variables see paragraph 6.1.

At start pre-test measurements (T0) will take place. After 10 weeks post-test measurements (T1) will take place. These post-test measurements will be the baseline measurements before entering the intervention condition. After 10 weeks final measurements (T2) will take place. Treatment As Usual (TAU) will be continued for all subjects in all periods.

### **3.2 Design rationale**

In the absence of an appropriate control game a wait list control design was chosen. This design allows to assess the effect of the intervention as add-on to standard care while controlling for potential external confounders. Allocation to treatment group will be done through an automated randomisation process to avoid introduction of bias in treatment allocation. Even though the trial will be open-label, efforts will be made to keep the assessor blinded to the treatment allocation during the trial to avoid bias in the assessment of subject outcome.

### **3.3 Duration/setting**

As soon as the trial has been approved by the Independent Review Board/ Independent Ethics Committee (IEC/IRB) according to local standards screening visits can take place. Screening and measurements (T0, T1 and T2) will be taken at the research sites in the morning with a maximum time slot of 14.00 am. It is important to test children in the morning because they appear to be more concentrated especially if they are on medication. In addition, this will keep the variation between children low. Between the T0 and T1 visit and between the T1 and T2 visit the period should be 10 weeks in length (with a recommended visit window of + 7 days). For study visits that are unable to be held within the recommended hours and visit window time frame, the visit should be conducted as closely as possible to the protocol-specified study visit timing, but the period in between visits cannot be shorter than 10 weeks. All subsequent visits should be scheduled based on the date of the T0 measurement, not the date of the rescheduled visit. The questionnaires for the parent/legal guardian will be available on laptop, and offered in a quiet surrounding. The investigator will emphasize that it is important that the questionnaires are filled out by the same parent on all measurement moments. The questionnaires and tasks for the child will be performed in a separate quiet room. Tasks for the child will be taken at the same time of day on all three measurements moments (T0, T1 and T2). The questionnaires for the teachers are presented online, during three measurements occasions (T0, T1 and T2). They can fill these out at work or at home. The HealSeeker game is web based, and therefore accessible at home using a unique log-in name and password.

### **3.4 Measurements**

To measure the effects of HealSeeker, this study uses both questionnaires and neuropsychological tasks administered to the child, and several questionnaires and checklists administered to their parents/legal guardians and teachers. Whilst playing HealSeeker, useful parameters for planning, time management and social skills will be saved in a computer database attached to the HealSeeker. First of all screening of subjects will take place, where informed consent will be signed and will be evaluated whether all in/exclusion criteria are fulfilled. If possible screening and T0 measurement will take place at the same visit. Measurements will take place at three different time intervals (T0, T1 and T2). More information concerning the measuring instruments used, and primary and secondary outcome variables is provided in paragraph 6.1: Study parameters/endpoints. The time and event schedule is illustrated in Table 1.

Table 1. *Time and event schedule.*

|                                                                                    | Week 0                                             | Week 0                              | Week 10         | Week 20         |
|------------------------------------------------------------------------------------|----------------------------------------------------|-------------------------------------|-----------------|-----------------|
| Study Procedure                                                             | Screening / T0 Measurements prior to randomization | T0 measurements after randomization | T1 measurements | T2 measurements |
| Screening / Administrative (Investigator / site personnel)                         |                                                    |                                     |                 |                 |
| Informed consent/assent (ICF) a                                         | X                                                  |                                     |                 |                 |
| Demographics                                                                       | X                                                  |                                     |                 |                 |
| Diagnostic interview (DSM-IV diagnosis ADHD)                                       | X                                                  |                                     |                 |                 |
| Intelligence WISC-III-NL (only if necessary) b                          | X                                                  |                                     |                 |                 |
| Inclusion/exclusion criteria                                                       | X                                                  |                                     |                 |                 |
| Randomize c                                                             |                                                    | X                                   |                 |                 |
| Adverse Events                                                                     |                                                    | X                                   | X               | X               |
| Concomitant therapy regarding ADHD                                                 |                                                    | X                                   | X               | X               |
| Parents                                                                            |                                                    |                                     |                 |                 |
| General questionnaire                                                              |                                                    | X                                   |                 |                 |
| Severity of symptoms (VvGK) (Parents / Legal Guardian)                             |                                                    | X                                   |                 |                 |
| Time management (self constructed questionnaire and It's About Time questionnaire) |                                                    | X                                   | X               | X               |
| BRIEF (planning, organizing, working memory subscale)                              |                                                    | X                                   | X               | X               |
| Social skills (subscale SSIS-RS)                                                   |                                                    | X                                   | X               | X               |
| Game experience of the child                                                       |                                                    | X                                   |                 |                 |
| Satisfaction HealSeeker (self constructed questionnaire) de             |                                                    |                                     | X d  | X e  |
| Children                                                                           |                                                    |                                     |                 |                 |
| Planning (neuropsychological task)                                                 |                                                    | X f                      | X               | X               |
| Social skills (SCVT)                                                               |                                                    | X f                      | X               | X               |
| Working memory (neuropsychological task)                                           |                                                    | X f                      | X               | X               |
| Self-efficacy (self constructed questionnaire)                                     |                                                    | X f                      | X               | X               |
| Satisfaction HealSeeker (self constructed questionnaire) de             |                                                    |                                     | X d  | X e  |
| Teacher                                                                            |                                                    |                                     |                 |                 |
| Time management (self constructed questionnaire)                                   |                                                    | X                                   | X               | X               |
| Social skills (subscale social skills rating scale)                                |                                                    | X                                   | X               | X               |
| BRIEF (planning, organizing, working memory subscale)                              |                                                    | X                                   | X               | X               |

aInformed assent applicable for children of 12 years old.

bOnly necessary if no intelligence test results are available of 2 years prior to screening.

cRandomize after all in/exclusion criteria fulfilled and study procedures above.

and VvGK (Parents / Legal Guardian) are performed.

dSatisfaction HealSeeker at T1 only for parents and children who played HealSeeker in the first 10 weeks (immediate treatment group).

e Satisfaction HealSeeker at T2 only for parents and children who played HealSeeker in the second 10 weeks (delayed treatment group).

fTasks of the child at T0 may take place prior to randomization, when parent is interviewed for diagnosis.

*Screening/T0 measurements prior to randomization*

Potential subjects will be seen at a screening visit (T0 visit), at which informed consent will be obtained from their both parents/legal guardians. From children of 12 years informed consent will be obtained. To confirm the inclusion and exclusion criteria and to gather general information about the child the following measurements will be done during the screening phase:

- Intelligence (only if necessary, using WISC-III-NL)
- DSM-IV diagnosis ADHD and co morbidity (using K-SADS and parent interview)

*T0 Measurement after randomization/T0 Visit*

After screening measurements, but at the same visit, children who meet the enrolment criteria will directly continue with T0 measurement (if possible). HealSeeker will be explained to children and their parents/legal guardians. To assess the level of skills at baseline measurement, the following measurements will be done:

Parent/legal guardian:

- General questionnaire
- Severity of problems (using VvGK)
- Time management (using a self-constructed questionnaire and the It's about time questionnaire)
- Planning (using the planning and organising subscale of the BRIEF)
- Social skills (using a subscale of the SSIS-RS)
- Working memory (using the working memory subscale of the BRIEF)
- Game experience of the child (using a self-constructed questionnaire)

Children:

- Planning (using a neuropsychological task; tower test)
- Social skills (using SCVT)
- Working memory (using a neuropsychological task; chessboard task)
- Self-efficacy (using a self-constructed questionnaire)

Teacher:

- Time management (using a self-constructed questionnaire)
- Planning (using the planning and organising subscale of the BRIEF)
- Social skills (using a subscale of the SSIS-RS)
- Working memory (using the working memory subscale of the BRIEF)

The teacher will be approached via a electronic news letter and asked to fill out some questionnaires about the participating child. They can access the questionnaires online through a link provided in an email. After T0 measurements children will be randomized in a 1:1 to immediate or delayed treatment group.

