## **6.2 Randomisation, blinding and treatment allocation**

Randomisation will be used to minimize bias in the assignment of subjects to treatment groups to increase the likelihood that known and unknown subject characteristics (e.g., demographic and baseline characteristics) are equally balanced across treatment groups (1:1), and to enhance the validity of statistical comparisons across treatment groups.

The randomization list will be stratified by site and gender using randomly permuted blocks.

Randomisation to the immediate and delayed treatment group condition will occur after collection of baseline data and confirmation of eligibility in the web-based ECD system.

The randomization process will be automated and based on a pre-specified computer-generated randomization list. A randomization number will be assigned online using the next available number on the randomization list corresponding with the site and gender of the subject. The trial will be open-label. Due to the nature of the intervention and time frame, it will be obvious for participants, their parents and teachers and the site staff to which treatment group they are allocated. All efforts are made to keep the assessor blind. If a child spontaneously tells the assessor his or her treatment condition, this will be registered.

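### Table 1 and a heading in Section 3.4 place the parent baseline for all three primary outcomes after randomisation, while the end of the Section 3.4 T0 text and Section 6.2 place it before

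*Protocol*

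**What the plan says.** Table 1 (Section 3.4) splits Week 0 into two columns, one for screening and T0 procedures before randomisation and one headed "T0 measurements after randomization". The parent rows for time management, BRIEF and SSIS have their T0 mark only in the second column. Section 6.1.3 takes all three primary outcomes from these parent ratings. The text heading above the list of T0 questionnaires reads "T0 Measurement after randomization/T0 Visit". Footnote f makes one exception: "Tasks of the child at T0 may take place prior to randomization, when parent is interviewed for diagnosis". It is attached to the child rows only.

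The opposite order appears twice. The T0 text of Section 3.4 ends: "After T0 measurements children will be randomized in a 1:1 to immediate or delayed treatment group". Section 6.2 says: "Randomisation to the immediate and delayed treatment group condition will occur after collection of baseline data and confirmation of eligibility".

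Section 6.2 also states that the trial is open label and that parents will know the group. Section 8 compares change from T0 to T1 by ANCOVA with baseline as covariate.

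**The concern.** All three primary outcomes are parent ratings, and the comparator is a 10-week wait. A parent who already knows whether the child plays now or waits may answer the baseline form differently. A covariate measured after allocation is protected by randomisation only if knowledge of the allocation does not affect it. If it is affected, the adjustment carries the difference into the treatment estimate, and a change score carries it in full. Keeping the assessor blind does not help, because the parent supplies the rating. An analysis plan cannot repair it either, because the order of procedures is settled at the visit.

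**Working it through.** **1. The statements side by side**

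| Place in protocol | Order for the parent primary questionnaires |
|---|---|
| Table 1, column and row placement | After randomisation |
| Section 3.4, heading over the T0 list | After randomisation |
| Table 1, footnote f | Lets only the child tasks come earlier |
| Table 1, footnote c | Asks for eligibility, the procedures above the randomisation row and, it appears, the VvGK first; does not name these questionnaires |
| Section 3.4, end of T0 text | Before randomisation |
| Section 6.2 | Before randomisation |

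Footnote c is interrupted by a break in the text as read, so little weight is put on it. The column heading, the row placement, the text heading and footnote f give the same result without it. The conflict is therefore within Section 3.4 as well as between Table 1 and Section 6.2.

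**2. The plan's own sample size figure (Section 4.5)**

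Inputs: SD of change 16, difference 8, 78 per group, 5% two-sided, stated power 87%.

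- Standard error = 16 × √(2/78) = 2.56.
- Power ≈ Φ(8/2.56 − 1.96) = 87.7%; the two-sample t calculation gives 87.3%.

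The stated figure reproduces, and it does not depend on the order of procedures.

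**3. Illustration of what a shifted baseline would do**

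The protocol gives neither a reporting shift nor a T0–T1 correlation, so both are assumed. Let knowledge of the allocation move the mean T0 time-management rating by s points between arms and leave T1 unaffected. Take equal variances at T0 and T1, so that the ANCOVA slope equals the correlation r. Then:

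- size of the ANCOVA bias = r × s, with sign opposite to the shift;
- residual SD = 16 × √((1 + r)/2), which is 12.90, 13.86 and 14.75 for r = 0.3, 0.5 and 0.7;
- standard error = residual SD × √(2/78);
- per-test type I error (unadjusted 5% level) = the two-sided rejection rate when the test statistic is shifted by bias/standard error.

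| r | s = 2: bias; type I error | s = 4: bias; type I error |
|---|---|---|
| 0.3 | 0.6 points; 6.0% | 1.2 points; about 9% |
| 0.5 | 1.0 points; 7.4% | 2.0 points; 14.7% |
| 0.7 | 1.4 points; 9.1% | 2.8 points; 22.0% |

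For r of 0.5 to 0.7 the bias runs from 1.0 to 2.8 points, that is 1.0/8 = 12.5% to 2.8/8 = 35% of the planned difference. These rows show how a shift would propagate. They do not estimate a shift.

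**The case against.** The strongest reply is that the protocol already contains the sound order. The two full-sentence statements about T0 as a whole, including the one in the section devoted to randomisation, put baseline first. The second Week 0 column is also not a strict sequence. It holds the randomisation row itself, the child tasks that may come earlier, and the VvGK, which footnote c appears to require beforehand. On this view the column label is loose drafting.

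Much of that stands. A reader might infer from Table 1 that the trial plans an allocation-aware baseline and that the primary estimates will be biased. The protocol does not support this. Bias needs three things together: a site follows Table 1 rather than Section 6.2, the family is told the allocation before completing the forms, and parents in the two arms then shift their ratings differently. No section says when families are told, and nothing documents such a shift. Nor does the text suggest that the game starts before baseline: Section 5.2 starts play in the first group after the baseline measurements.

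The objection does not remove the contradiction. The protocol does not rank Section 6.2 above its own visit schedule. The text heading repeats the table's order, and the one explicit exemption covers the child tasks and not the parent questionnaires. Sites that read the protocol differently would mix pre- and post-allocation baselines in one analysis. Parents will also know the group at T1, but that is inherent in the stated design, whereas a post-allocation baseline is avoidable.

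**Conclusion.** The contradiction is certain. It lies in current text and concerns the baseline of every primary outcome. The bias is conditional: it arises only where Table 1 is followed, the allocation is disclosed before the forms are completed, and ratings respond to it. Its direction is unknown, so it could exaggerate or hide a benefit. The figure of 1.0 to 2.8 points rests wholly on an assumed 2 to 4 point shift and an assumed slope of 0.5 to 0.7, and the type I error rates above rest on the same kind of assumption. No sample size figure changes. The reason to act now is that a baseline collected in the wrong order cannot be recovered later.

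**What to change.** Reconcile Table 1 and the heading with the end of the Section 3.4 T0 text and with Section 6.2:

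- Move the parent and child T0 outcome rows to the column before randomisation, and place the randomisation row after them.
- Rename the Section 3.4 heading so that it no longer puts the T0 measurements after randomisation.
- Reword footnotes c and f to say that the randomisation number is assigned only after the parent T0 questionnaires and the child T0 tasks are completed.
- State whether the teacher T0 questionnaires come before or after randomisation. They sit in the same column and are completed online through an emailed link, so the reference in Section 6.2 to collected baseline data is unclear for them. They are not primary.

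The cost is a wording change to one table, one heading and two footnotes, plus one sentence on teachers. The visit, the questionnaires and the family's burden stay the same. No electronic lock on the case report form is needed; it would be a system change, and it would fit poorly with Section 10.6, which allows paper source for the child tasks.
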